#### fNIRS assessments

This experiment used a portable near-infrared functional brain imager (NirSmart, Danyang Huichuang Medical Equipment Co., Ltd., China) to record the cortical activation state. Our equipment consisted of 13 light sources and 15 detectors, making up a total of 35 channels, with an average distance between light sources and detectors of 2.7 cm. Reference was made to the international 10–20 system for localization [33], with the Cz point and Fpz point marked as standard localization points.

Subjects carry a special backpack to carry the fNIRS mainframe which transmits the data to the computer via wireless mode. Based on previous studies, the present study selected bilateral DLPFC, M1, and S1, which have been shown to be associated with sensory function, for testing. In this study, we examined bilateral PFC and S1 brain regions associated with sensory functions, and their channels corresponded to cortical distributions in CH17, CH20, CH22, CH26, CH27, CH31, CH36, CH43, CH48, and CH49. During the fNIRS test, the room temperature is kept at a comfortable constant, and the room is kept quiet. The patient is guided by audio to remain quietly in a seated position (Fig. 4) and is informed that self-activity and communication are prohibited during the test. Measurements will be taken in the resting state and in the shoulder joint external rotation and abduction state, three times in each state and averaged.

**Fig. 4 Fig4:**
[figure not shown]
The fNIRS test process

Data analysis for this experiment focused on oxyhemoglobin (HbO) concentration as a marker of cortical activation, as it is the most sensitive and reliable indicator of changes related to regional brain oxygenation movements. The NirSpark software is used to analyze the fNIRS data. Oxygenated hemoglobin concentrations for each region are superimposed and averaged to produce results for that region. By analyzing the trend of each parameter, it is possible to see the variation of each channel in the task state versus the resting state.

#### Upper limb Fugl-Meyer scores

The Fugl-Meyer motor function assessment with the upper limb contained 33 items for assessment. This test only requires the assessment of the patient’s upper limb motor function: (1) presence or absence of reflex activity; (2) flexor synergism; (3) extensor synergism; (4) activity with synergism; (5) activity out of synergism; (6) hyperreflexia; (7) wrist stability; (8) elbow extension with 30° of shoulder flexion; (9) fingers; (10) synergism and speed (finger finger-nose test 5 times in a row) 10 items, each with different sub-items, each with a score of 0–2.

#### Shoulder ROM

Passive anterior flexion (0° to 170°)

Position: sitting or supine (humerus in neutral position).

Goniometer placement: the axis is located at the lateral crest of the humerus, the fixed arm is parallel to the trunk, and the movable arm is parallel to the humerus.

2.Passive abduction (0° to 180°)

Position: seated or prone (humerus in externally rotated position).

Goniometer placement: the axis is located posterior to the acromion, the fixed arm is parallel to the trunk, and the movable arm is parallel to the humerus.

3.Passive external rotation (0° to 90°)

Position: sitting or supine (90° elbow flexion, 90° shoulder abduction, forearm rotation posterior).

Protractor placement: axis at the eminence, fixed and mobile arms parallel to the forearm. Note: The fixed arm remains in its original position parallel to the ground when the shoulder is externally rotated, while the mobile arm follows the forearm.

#### Spasticity (MAS)

This is a scale for grading muscle tone and assessing spasticity based on passive joint movement resistance. The speed of movement is the completion of a joint movement in 1 s. There are 5 levels: grade 0, no muscle tone; grade 1, a slight increase in muscle tone, passive flexion, and extension of the affected part with minimal resistance or sudden catch and release at the end of the joint range of movement; grade 1 + , a mild increase in muscle tone with sudden catch in the second 50% of the joint range of movement and then minimal resistance in the second 50% of the joint range of movement; grade 2, a more pronounced increase in muscle tone with a more pronounced; grade 3, severe increase in muscle tone, with difficulty in passive movement; grade 4, tonicity, with stiffness and immobility of the affected part during passive flexion and extension.

### Participant timeline {13}

The participant timeline is presented in Table 1.

**Table 1 Tab1:**
[figure not shown]
Participant timeline

*VAS*, Visual analogue scale

^#^Functional near-infrared imaging examination includes the primary motor area (M1), dorsolateral prefrontal area (DLPFC), and primary sensory area (S1)

### Sample size {14}

This study is a randomized controlled trial with botulinum toxin injections in the experimental group and glucocorticoid (tretinoin acetate) injections in the control group. The main regression indicator observed is the VAS pain score.

In this study, the sample size will be calculated with reference to similar relevant literature and pre-experimental results. The sample size will be calculated using two independent sample mean validity tests using the G-Power version 3.1.2 software. It is assumed that the means of the two groups are equal at baseline, that there is a 1-point difference in VAS pain score between the two groups at the first post-treatment assessment, and that the standard deviation of the two groups was 1.4, which should be consistent at each subsequent assessment, measured as an effect size (i.e., Cohen *d*, 0.71). Based on these magnitudes, alpha = 0.05 two-tailed is set. To achieve 80% efficacy, 32 patients per group will be counted as study subjects. To compensate for potential loss to follow-up, approximately 20% of patients will be added, with a final inclusion target of 78 patients (39 in each group).

### Recruitment {15}

Participants will be recruited through the following: (1) advocacy by participating clinical teams for presenting patients with hemiplegic shoulder pain, (2) mobilizing the surrounding community hospitals to publicize, (3) posting recruitment advertisements in hospitals and surrounding communities, (4) use social media to post and disseminate e-recruitment advertisements.

## Assignment of interventions: allocation

### Sequence generation {16a}

This study, subjects will be divided into experimental and control groups in a 1:1 ratio using a completely randomized method. Random numbers are generated using the SPSS software, a random allocation table will be prepared, and the drugs are blindly packed according to the random allocation table. The subject number corresponded to the corresponding random number, drug label, and drug name. Everything is to be written on a piece of paper and sealed in an envelope.

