## Background and rationale {6a}

Hemiplegic shoulder pain (HSP) is a relatively common complication after stroke, with a prevalence of 16–84% [1]. HSP usually occurs within 12 weeks after stroke, which can seriously affect the recovery of upper limb motor function [2] and reduce the quality of life of patients [3]. Previous studies have shown that the pathogenesis of HSP is considered to be multi-factor, and paralysis is considered as the main cause of shoulder pain [4]. The current academic opinion suggests that HSP is more likely to be caused by neuropathic pain, which is caused by dysfunctional transmission and signal processing of the nervous system [5, 6].

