### Objectives {7}

The primary aim is as follows: to investigate whether shoulder joint cavity injection of botulinum toxin compared with corticosteroids (tretinoin acetate) significantly improves shoulder pain in patients with HSP without biceps tendinitis or acromionic bursitis.

The secondary aims are as follows: in patients with HSP without tendon synovitis or acromioclavicular bursitis, does shoulder joint cavity injection of botulinum toxin type A significantly affect cerebral hemodynamics, improve Fugl-Meyer upper limb motor function, improve passive shoulder motion, and improve Ashworth scale scores compared to glucocorticoids (tretinoin acetate)?

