### Eligibility criteria {10}

Inclusion criteria:Conform to the diagnostic criteria of stroke in Diagnostic Essentials of Major Cerebrovascular Diseases in China 2019; the diagnosis was confirmed by craniocerebral CT or MRI examination.First onset of stroke, age 18–80 years old, duration ≤ 6 months.Visual analog scale (VAS) for pain during passive abduction or external rotation of shoulder joint ≥ 4 points.Shoulder joint drug injection was not performed in half a year.The modified Ashworth scale for external rotation or abduction of shoulder joint was rated between 0 and 1 + Ultrasound of shoulder joint: the patient showed no accompanying acromion-deltoid slide bursitis or biceps brachialis tendinitis.There are no other bone, joint, and muscle diseases or other neurological diseases that significantly affect motor function.No obvious communication and understanding obstacles, able to carry out normal communication and cooperate with the completion of the experiment.The vital signs are stable and can cooperate with the examination.

Exclusion criteria.llergy to botulinum toxin or glucocorticoid.Intra-articular glucocorticoid or botulinum toxin injection of shoulder in the last 6 months.Previous history of shoulder joint surgery, frozen shoulder, rotator cuff injury, and shoulder joint trauma.Have other diseases more painful than hemiplegia shoulder pain.Active malignant tumors.Coagulopathy, diabetes mellitus, gastric ulcer, infection (within the last 6 months).Currently taking oral glucocorticoids, non-steroidal anti-inflammatory drugs, or immunosuppressive drugs.Pregnant and lactating women.With severe cognitive impairment, Minimum Mental State Examination (MMSE) score less than 21.Those who have not signed the informed consent.

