## Statistical methods

### Statistical methods for primary and secondary outcomes {20a}

All statistical inferences will be performed by two-sided test, the test level of statistical significance is set as 0.05, and the confidence interval of parameters is 95%. The count data describe the number of cases and percentage, and the measurement data describe the mean, standard deviation, minimum, maximum, median, and 25th and 75th quantiles. The counting data give the frequency distribution and the corresponding percentage. Qualitative data give the number of cases of positive rate, positive number, and denominator.

Shapiro–Wilk test will be used to verify the normality of the variables. For normally distributed variables, continuous variables are represented by “mean ± standard deviation”; for data that is not normally distributed, it is represented by “median, interquartile.”

In the analysis of baseline data, the independent sample *t* test will be used to compare the normal distribution between the measurement data groups. The non-normal distribution data are presented with median and interquartile intervals. Mann–Whitney *U* test will be used to compare ordered categorical variables between groups.

Repeated measures ANOVA will be used to study the independent effects, main effects, and interactions of time and grouping. *p* < 0.05 is considered statistically significant. Intentionality and protocol sets will be used to analyze primary and secondary outcomes. The results of intentionality treatment analysis are compared with those of protocol set analysis to determine whether the results are consistent. Missing data are processed as multiple imputation. Adverse events will be listed and analyzed using chi-square tests or Fisher precision tests. We analyzed test results using the IBM SPSS24.0 software.

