### Methods for additional analyses (e.g., subgroup analyses) {20b}

Sub-group analyses are not foreseen.

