We will primarily attempt to quantify the relief of the patient’s shoulder pain using VAS. To observe the improvement in pain in relation to the oxyhemoglobin concentration in the corresponding brain regions, we will apply the fNIRS to quantify the corresponding brain regions of the patients. fNIRS is particularly suitable for predicting changes in pain intensity. Quantifying changes in cortical activation associated with nociception by fNIRS. Related studies have also confirmed the involvement of the PFC and S1 brain regions in pain processing [41]. We hoped that changes in blood flow activity in the corresponding brain regions would provide objective data to support shoulder pain relief to complement patients’ subjective report of pain scores. The agreement between subjective perception of pain and objective HbO in subjects measured using fNIRS is more consistent. The Fugl-Meyer assessment examined whether pain reduction improves motor function, an important functional outcome in post-stroke rehabilitation.

A limitation of this study is the lack of a control group receiving sham injections of placebo. The short follow-up period of 4 weeks is another limitation. Long-term outcome data could help assess the durability of injection pain relief. In conclusion, this trial is research to assess the effectiveness and security of ultrasound-guided botulinum toxin injections in the treatment of patients with HSP. The results of this research will be important for clinicians to prescribe as a treatment option, and the scientific and methodologically rigorous design of this trial is expected to provide a reliable reference for the future application.

Future studies could explore intra-articular botulinum toxin injections in combination with rehabilitation programs (e.g., physiotherapy or occupational therapy) to optimize functional outcomes. Other neuroimaging methods, such as fMRI, may also provide further insights into the central mechanisms of hemiplegic shoulder pain.

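### Time since stroke, known for every patient, is used in neither the allocation nor the stated model, which costs precision on the secondary motor and fNIRS outcomes and leaves their associations with pain open to confounding

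*Protocol article*

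**What the plan says.** Eligibility criteria {10} caps time since stroke and gives no lower limit: "First onset of stroke, age 18–80 years old, duration ≤ 6 months". Sequence generation {16a} fixes the allocation: "subjects will be divided into experimental and control groups in a 1:1 ratio using a completely randomized method". Neither blocking nor stratification is mentioned there or in the two allocation items that follow.

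The only outcome model named is in Statistical methods {20a}: "Repeated measures ANOVA will be used to study the independent effects, main effects, and interactions of time and grouping". Time in that sentence is the visit (baseline, 1 week, 4 weeks), not time since stroke. On further analyses, item {20b} says: "Sub-group analyses are not foreseen".

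The secondary question in Objectives {7} is whether botulinum toxin will "significantly affect cerebral hemodynamics, improve Fugl-Meyer upper limb motor function, improve passive shoulder motion, and improve Ashworth scale scores compared to glucocorticoids". Beyond the arm comparison, the Discussion gives a causal reading of one outcome: "The Fugl-Meyer assessment examined whether pain reduction improves motor function". The abstract likewise expects the results to show how change in pain goes with change in cortical blood flow and in motor function.

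**The concern.** The entry window can mix patients at quite different stages of recovery. If motor score or cortical activity changes over 4 weeks at a rate that depends on time since stroke, that dependence has two consequences under the plan as written.

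First, variation in recovery rate stays in the error term of the Fugl-Meyer and fNIRS comparisons, and a chance surplus of early patients in one arm goes uncorrected. The baseline visit in a repeated measures ANOVA deals with differences in starting level. It does not deal with differences in the rate of change.

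Second, the associations between pain change and motor or HbO change are made across patients, not between randomised groups. If recently affected patients improve on several measures together, those changes will correlate even if pain relief has no effect on movement or cortical activity.

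The primary VAS comparison is not the target of this point.

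**Working it through.** **The plan's own figure.** Sample size {14} uses a 1-point VAS difference, SD 1.4, two-sided 0.05 and 80% power. d = 1/1.4 = 0.714. The two-sample t test (noncentral t) gives n = 31.76, so 32 per group, with power 80.3%. Adding 20%: 32 × 1.2 = 38.4, so 39 per group and 78 in total. Both stated figures reproduce. They concern VAS; the documents give no such calculation for the secondary outcomes.

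**Inputs for the check.** From the documents: 39 per arm (32 if the full loss allowance is used up) and a two-sided 0.05 test. Assumed, because the documents do not give them: a true effect of 0.5 SD, and a correlation r between time since stroke and 4-week change of 0.3 to 0.7.

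**Chance imbalance.** The SE of the standardised difference in mean time since stroke is √(2/39) = 0.226.
- P(imbalance > 0.25 SD) = 2 × [1 − Φ(0.25/0.226)] = 27%
- P(imbalance > 0.40 SD) = 2 × [1 − Φ(0.40/0.226)] = 8%
- With 32 per arm (SE 0.25): 32% and 11%

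**Effect on the tests.** Simulation with 39 per arm and 40,000 trials per setting, comparing an unadjusted t test with ANCOVA on time since stroke:

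| r | Type I, all trials, unadjusted | Type I given imbalance > 0.25 SD, unadjusted | Power, all trials, unadjusted | Power, all trials, adjusted | Power if imbalance > 0.25 SD runs against the better arm: unadjusted / adjusted |
|---|---|---|---|---|---|
| 0 | 5.0% | 5.0% | 59% | 59% | 58% / 57% |
| 0.3 | 5.0% | 6.9% | 59% | 62% | 39% / 61% |
| 0.5 | 5.0% | 10.1% | 58% | 70% | 27% / 70% |
| 0.7 | 4.7% | 13.3% | 59% | 86% | 13% / 85% |

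Adjusted type I error is about 5% throughout, both overall and given the imbalance. At r = 0 the covariate costs almost nothing.

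**The same thing in Fugl-Meyer points, as illustration.** Assume that half the patients are early, that the early half gains 4 to 8 points more in 4 weeks, and that the remaining SD of change is 5. The variance due to stage is g²/4 = 4 to 16.
- Part of the arm difference due to imbalance, 95% range: ±1.96 × √(2 × 4/39) = ±0.89 to ±1.96 × √(2 × 16/39) = ±1.78
- Ordinary sampling noise: ±1.96 × √(2 × 25/39) = ±2.2
- Both together, which is what the unadjusted interval already shows: ±1.96 × √(2 × 29/39) = ±2.4 to ±1.96 × √(2 × 41/39) = ±2.8
- Equivalent r: √(4/29) = 0.37 to √(16/41) = 0.62, inside the range tabulated above

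No comparable figure can be given for HbO.

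**Associations.** Suppose that pain change and motor change each correlate r with time since stroke and are otherwise unrelated. Their correlation is then r × r = 0.09, 0.25 or 0.49 for r = 0.3, 0.5 or 0.7. With 78 patients, a correlation reaches two-sided p < 0.05 at 1.992/√(1.992² + 76) = 0.22. At r = 0.5 or more, shared recovery alone would therefore produce a correlation above the significance threshold.

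**The case against.** The strongest reply is that nothing here is an error. Simple randomisation is valid, recovery occurs in both arms and balances in expectation, and any prognostic factor that is left unstratified looks worse once one conditions on a bad draw. That stands. A reader might infer that spontaneous recovery can mimic or mask a drug effect in a way that undermines the arm comparison. The documents do not support this: the error rate over all randomisations is about 5%, and the extra spread is already in the unadjusted confidence interval. A spurious arm difference in points and an inflated residual variance are one effect, not two.

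Several other tempting readings also fail:
- That patients enter in the first days after stroke. The text only lacks a lower limit. The requirements for VAS of at least 4, stable vital signs and adequate cognition may delay entry.
- That 12 weeks is a natural recovery cut-point. The background sentence, "HSP usually occurs within 12 weeks after stroke", concerns onset of pain, not motor recovery.
- That an untreated arm is needed. The objectives compare two drugs, and the Discussion already lists the missing placebo group as a limitation.
- That unequal arms are likely. Unrestricted draws would give exactly 39/39 in only about 9% of trials, but a prepared allocation table with 39 in each group can equally be a list of fixed size.

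A further reply is that covariates and the method for the associations may sit in a statistical plan that is not shown. This is fair, and their absence is not the finding. But allocation is settled in the protocol and cannot be repaired by an analysis plan, and the article does state a model, with visit and group only.

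**Conclusion.** The point holds as a design weakness confined to the secondary motor and fNIRS outcomes and their associations with pain. It is not a source of bias in the trial. As written, time since stroke enters neither allocation nor model. For the arm comparisons, the loss is negligible if r is near 0, small at 0.3 and substantial at 0.7, where power for the assumed 0.5 SD effect would be 86% adjusted against 59% unadjusted. An imbalance large enough to matter has roughly a one in four chance. For the associations the concern is of a different kind: randomisation gives no protection, so a correlation between pain change and motor or HbO change could not be read as an effect of pain relief without at least this adjustment. The size of all of this rests on r and on the 0.5 SD effect, both assumed. That recovery depends on time since stroke is itself an assumption here, not a statement in the protocol.

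**What to change.** Prespecify time since stroke as a covariate, preferably continuous, in the Fugl-Meyer and fNIRS models. In a repeated measures model it must enter with its interaction with visit, because a main effect alone adjusts average level and not change. The alternative is an ANCOVA of the follow-up value on baseline value, group and time since stroke. Make the same adjustment in every pain–motor or pain–HbO association, and describe these as associations. Fix this before any look at data by arm, including the interim analysis planned at 39 patients.

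If the allocation list is not yet in use, replace simple randomisation with permuted blocks of varying size, stratified by time since stroke at a cut-point that the investigators choose and justify. Trial status gives 1 March 2024 as the start of recruitment, so this may no longer be possible; the covariate then does most of the work.

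The cost is one extra model term and, if stratified, a second set of numbered packs. No new data and no additional patients are needed, and the sample size does not change.

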### Concealment mechanism {16b}

Allocation concealment will be ensured; the randomization code will not be generated until the patient has completed all baseline measurements. The drugs will be packaged and sealed uniformly by a person unrelated to the trial. Each of the random number assigned are to be written on a piece of paper and enclosed in a sealed envelope.

### Implementation {16c}

Trial assistants will generate and maintain the allocation sequence but will not be involved in the overall treatment process. The principal investigator will group participants according to their number. Participants will not be allowed to change their group assignment after allocation.

